### Study visits and follow‐up

2.8

All subjects will be followed up at 1 month (±7 days), 6 months (±7 days), and 12 months (±7 days) in the outpatient clinic, and at 2 weeks (±7 days), 2 months (±7 days), and 3 months (±7 days) by telephone. The patients' primary and secondary endpoints, (severe) adverse events, medications, and the results of the tests mentioned above will be carefully recorded during the follow‐up.

### Sample size determination and statistical analysis

2.9

The OPTIMA‐4 trial aims to simultaneously test the following two hypotheses of dabigatran‐based DATT in eligible patients: (1) clopidogrel is superior to ticagrelor regarding major bleeding and CRNMB events and (2) clopidogrel is noninferior to ticagrelor regarding the composite efficacy endpoint. According to the RE‐DUAL PCI trial, the anticipated incidence of annual efficacy endpoint is 18.9% in the arm of ticagrelor.^9^ We set a noninferiority margin ratio of 1.38 and *α* of .025 (one‐sided), 655 patients in each group are required to achieve a statistical power of 80%.^9^ Assuming that 11% of patients will be lost to follow‐up (1%) or drop‐out (10%), at least 736 patients are finally required for each randomized group. Then, the final sample size is estimated to be 1472. With this sample size, the anticipated power for the composite safety endpoints (14.5% and 21.2% in clopidogrel and ticagrelor groups, respectively) would be around 87.1%.^9^

Descriptive statistics will be used to summarize and analyze the baseline demographic characteristics (mean, SD, median, minimum, first quartile, third quartile, and maximum for continuous measures; frequency counts and percentages for categorical measures) of each treatment group; the Student *t* test or analysis of variance will be used for the comparison of continuous variables and *χ*
^2^ test for the comparison of categorical variables across treatment groups.

To control the type I error at one‐side 0.025 level, a hierarchical procedure for multiple testing will be used. The paradigm of the hierarchical procedure in OPTIMA‐4 trial is detailed below:
Step 1:Superiority of dabigatran combined with clopidogrel to dabigatran combined with ticagrelor concerning major bleeding and CRNMB is met at the one‐sided 0.025 level of significance.Step 2:Noninferiority of dabigatran combined with clopidogrel to dabigatran combined with ticagrelor for the efficacy endpoint is met at the one‐sided 0.025 level of significance.

If step 1 fails to meet statistical significance, step 2 will not be performed.

The primary endpoints will be treated as time‐to‐event endpoints, and the Kaplan–Meier method will be employed to estimate the cumulative incidences of endpoints by treatment group. The primary endpoints between the two groups will be compared using the Cox proportional hazards model with treatment as a fixed effect and adjusted for other covariates separately. The estimated hazard ratio (HR) and two‐sided 95% confidential interval (CI) or one‐sided 97.5% CI for the noninferiority test will be provided. For the noninferiority test in the composite efficacy endpoint, the noninferiority margin is 1.38 on the HR scale. The upper boundary of CI for the HR (one‐sided 97.5%) will be compared to this margin. All the above analyses will also be conducted in predefined subgroups. The secondary time‐to‐event endpoints will be analyzed using the methods mentioned above. All statistical analyses will be performed using SAS version 9.4 (SAS Institute Inc.).

The analysis sets are as follows: (1) full analysis set (FAS): according to the intention‐to‐treat principle, the FAS is defined as all patients being randomized who receive at least one dose of the assigned treatment; (2) per‐protocol analysis set (PPS): the PPS is a subset of FAS, which includes all randomized patients meeting the study eligibility criteria, without major protocol deviation (see Supporting Information: Appendix 5),^21^, ^24^ without using drugs or receiving treatments that may interfere with the evaluation of efficacy, and accomplishing all efficacy assessments after randomization; and (3) safety set (SS): the SS includes all randomized patients with at least one safety assessment after randomization. The analysis of primary endpoints will be performed on both FAS and PPS, with FAS analysis as the primary analysis. Consistency of the results on primary endpoints between FAS and PPS will demonstrate the robustness of the conclusion. Safety analyses will be performed on the SS.

Subgroup analyses are planned across major subgroups by age, sex, body mass index, diabetes, ACS diagnosis, the Synergy between Percutaneous Coronary Intervention with Taxus and Cardiac Surgery (SYNTAX) score, and CHA_2_DS_2_‐VASc score (see Supporting Information: Appendix 6).

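### The 655 per arm matches a risk-ratio calculation, but the primary noninferiority test is a Cox hazard ratio against 1.38, whose power is about 72% to 77% and not 80%

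*Protocol article*

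**What the plan says.** Everything relevant stands in section 2.9 of the protocol article (Sample size determination and statistical analysis).

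- **Sizing.** The rate is taken from an earlier trial: "the anticipated incidence of annual efficacy endpoint is 18.9% in the arm of ticagrelor". Then: "We set a noninferiority margin ratio of 1.38", with one-sided alpha 0.025. The scale of the ratio, the formula and a separate clopidogrel efficacy rate are not given. The result is that "655 patients in each group are required to achieve a statistical power of 80" per cent. An allowance of 11% (1% lost, 10% drop-out) raises this to 736 per arm, 1472 in all.
- **Analysis.** "The primary endpoints will be treated as time‐to‐event endpoints". "The primary endpoints between the two groups will be compared using the Cox proportional hazards model". For efficacy, "the noninferiority margin is 1.38 on the HR scale", and the upper one-sided 97.5% limit is compared with it.

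No target number of events is stated.

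**The concern.** The sample-size paragraph works from a 12-month proportion and an unnamed ratio; the analysis paragraph works from a hazard ratio. The same number, 1.38, is used for both. With events in about a fifth of patients, a risk ratio and a hazard ratio of 1.38 are not the same margin, and the two tests do not have the same precision for a given number of patients. A sample size that gives 80% power on one scale therefore need not do so on the other.

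The noninferiority comparison is one of the trial's two primary hypotheses and the one from which the sample size is derived. If the declared test has less power than stated, a true noninferiority would be missed more often than the plan admits, and a reader of an inconclusive result would misjudge how sensitive the trial was. Without an event target, a shortfall would not be visible while the trial runs.

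**Working it through.** **Inputs**

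- One-sided alpha 0.025 (z = 1.960), power 80% (z = 0.842), rate 18.9%, margin 1.38, 11% loss, 736 randomised per arm: section 2.9.
- Allocation 1:1: section 2.3. Follow-up of 12 months for each patient: abstract, Methods.
- Assumption: the true rate is 18.9% in both arms. The article gives no clopidogrel efficacy rate; its hypothesis is comparable efficacy.

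**Step 1. Reproduce 655.** Use the Farrington-Manning score test for a ratio of two proportions, R = 1.38.

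- Rates constrained to the margin: 0.2179 and 0.1579.
- s0 = √(0.2179 × 0.7821 + 1.38² × 0.1579 × 0.8421) = 0.651
- s1 = √(0.189 × 0.811 × (1 + 1.38²)) = 0.667
- Distance to the margin: 0.38 × 0.189 = 0.0718
- n = ((1.960 × 0.651 + 0.842 × 0.667) / 0.0718)² = 654.4, so **655 per arm**. Power at 655 is 80.0%.

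Then 655 / 0.89 = 736, which also matches. A Wald test of the log risk ratio gives 650. The hazard-ratio formulas give 802 (Schoenfeld) and 815 (Freedman). The stated safety power of 87.1% is also close to a two-proportion test with continuity correction at 655 per arm (87.3%).

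**Step 2. Compare the two margins at 18.9%.**

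- Hazard ratio 1.38: risk 1 − 0.811^1.38 = 25.1%, a risk ratio of 1.33.
- Risk ratio 1.38: risk 1.38 × 18.9% = 26.1%, a hazard ratio of ln(1 − 0.261)/ln(0.811) = 1.44.

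The declared hazard-ratio margin is the stricter one.

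**Step 3. Events needed by the declared test.**

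D = 4(1.960 + 0.842)² / (ln 1.38)² = 4 × 7.849 / 0.1037 = 302.6, so **303 events**.

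Per arm at 18.9%: 302.6 / (2 × 0.189) ≈ 801 evaluable patients.

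**Step 4. Power with the planned numbers.** Power = Φ(√(D/4) × ln 1.38 − 1.960). For 655 per arm, D = 2 × 655 × 0.189 = 247.6, and Φ(7.868 × 0.3221 − 1.960) = Φ(0.574) = 71.7%.

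| Per arm | Events | Power (formula) | Power (two Cox simulations, 4000 replicates each) |
|---|---|---|---|
| 655, all complete | 247.6 | 71.7% | 70.8%, 72.2% |
| 736, 11% leave during the year | 263 | 74.3% | 73.4%, 73.8% |
| 736, 1% lost | 277 | 76.4% | not run |
| 736, all complete | 278.2 | 76.6% | 76.5%, 75.7% |
| 801, all complete | 302.8 | 80.0% | 80.7%, 80.9% |

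**Step 5. Sensitivity.**

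- If 18.9% is read as an annual hazard, the 12-month risk is 1 − exp(−0.189) = 17.2% and power falls to 67.7% (655 per arm) or 72.7% (736 per arm).
- If the true 12-month rate were 12% or 10% (assumed values, not in the article), power with 655 to 736 per arm would be 52% to 57% or 45% to 50%.

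**The case against.** Five points can be made in the plan's defence.

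1. **The formula is not named.** That 655 comes from a risk-ratio test is an inference. This is correct. The match is exact, but the conclusion does not depend on it: however 655 was obtained, it does not give the Cox test 80% power when the arms have equal rates.
2. **Equal rates are assumed.** If clopidogrel were slightly better, with a true hazard ratio of about 0.96 (655 per arm) or 0.985 (736 per arm), the Cox test would reach 80%. The article states no such advantage, and equality is the assumption under which 655 reproduces.
3. **71.7% is too low for the primary analysis.** The full analysis set is primary, and patients who leave contribute time and events until they do. This stands: about 74% to 77% is the likelier range for that analysis. The 71.7% is the direct counterpart of the article's own claim for 655 patients. No retention scenario at 18.9% reaches 80%.
4. **Another hazard-ratio formula might give 655.** The nearest is 674: 303 events divided by the sum of 18.9% and 26.1%. It counts events as if clopidogrel were at the margin while computing power at a hazard ratio of 1. It is inconsistent, and it still is not 655.
5. **The decision rule is clear.** The test, scale, margin and limit are fixed, type I error is unaffected, and the stricter margin cannot cause a false claim of noninferiority. This also stands, and it limits the harm to power and to how the result is read.

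**Conclusion.** The statement is wrong as written. The declared noninferiority test does not have the 80% power claimed for 655 per arm: it has 71.7% with 655 evaluable per arm, about 74% with 736 randomised and 11% leaving over the year, and at most 76.6% with no loss at all. The type II error is therefore about 23% to 28% where 20% is stated, and the planned 248 to 278 events fall short of the 303 required.

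These figures assume 18.9% at 12 months in both arms, proportional hazards and no gain from covariate adjustment. Reading 18.9% as a hazard, or a lower true rate, makes the shortfall larger. The attribution of 655 to a risk-ratio calculation is inferred from an exact match; the power deficit is not.

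**What to change.** Correct the sample-size paragraph of section 2.9 and leave the trial as it is:

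- Say that the Cox test against a hazard ratio of 1.38 needs 303 primary efficacy events for 80% power at one-sided 0.025, assuming equal true rates.
- Say that 736 randomised (655 evaluable) per arm are expected to give about 248 to 278 events, and power of about 72% to 77% depending on retention.
- Report the observed number of events against 303 with the results.
- Keep enrolment at 1472 and the margin at 1.38 on the hazard-ratio scale. Do not move to a risk-ratio test to recover the 80%: at 18.9% this would loosen the margin to a hazard ratio of about 1.44.

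The cost is one paragraph and a less favourable stated power, with no extra patients. For comparison, restoring 80% by enrolment would need about 802 / 0.89 = 901 randomised per arm, or 1802 in all, which is 330 more than planned.

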### Endpoints

2.7

The primary efficacy endpoint of the OPTIMA‐4 trial is a composite of cardiovascular death, myocardial infarction, unplanned revascularization, ischemic stroke, and systematic thromboembolism during 12‐month follow‐up. The primary safety endpoint is major bleeding and clinically relevant nonmajor bleeding (CRNMB) defined by the International Society of Thrombosis and Hemostasis (ISTH) during 12‐month follow‐up.^20^ The composite secondary endpoint of net adverse events included all‐cause death (cardiovascular death, noncardiovascular death), acute myocardial infarction (fatal or nonfatal, Q‐wave or non‐Q‐wave), systemic thromboembolism, unplanned revascularization (target or nontarget vessel, target or nontarget lesion), stent thrombosis (possible, probable, definite), stroke (hemorrhage or ischemic) and bleeding (ISTH or Bleeding Academic Research Consortium [BARC] criteria) during 12‐month follow‐up.^20^, ^21^

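### One minus Kaplan–Meier, planned as the estimator of cumulative incidence, slightly overstates each arm's 12-month bleeding incidence because death from other causes is not part of that endpoint

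*Protocol article*

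**What the plan says.** Section 2.9 treats the primary endpoints as time-to-event outcomes and says that the Kaplan–Meier method "will be employed to estimate the cumulative incidences of endpoints by treatment group". It names no other estimator of absolute risk and does not say how a death outside the endpoint is handled.

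For the comparison, the same section says: "The primary endpoints between the two groups will be compared using the Cox proportional hazards model with treatment as a fixed effect". The effect measure is the hazard ratio with its confidence interval, and noninferiority is judged by the upper limit against 1.38. For the rest: "The secondary time‐to‐event endpoints will be analyzed using the methods mentioned above".

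Section 2.7 defines the endpoints:
- **Safety:** "The primary safety endpoint is major bleeding and clinically relevant nonmajor bleeding", by ISTH criteria over 12 months. Death from other causes is not a component.
- **Efficacy:** a composite that includes cardiovascular death but not noncardiovascular death. Section 2.7 also classes deaths of unknown cause as cardiovascular.
- **Secondary:** a net-adverse-events composite that includes all-cause death.

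**The concern.** Section 2.9 names both a target, the cumulative incidence, and an estimator, Kaplan–Meier. The two agree only when no patient can leave the risk set through an event that makes the endpoint impossible. A patient who dies without a qualifying bleed cannot bleed later. Censoring that patient treats the future bleeding risk as the same as in survivors, so one minus Kaplan–Meier describes a population in which nobody dies first. It is never below the true cumulative incidence.

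What is at stake is descriptive. The Discussion says that both a safety and an efficacy primary endpoint were chosen to weigh benefit against risk, and readers will do that with the absolute 12-month figures. More deaths compete with bleeding than with an efficacy composite that already counts cardiovascular and unknown-cause death. The two sides of that weighing would therefore be inflated unequally.

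**Working it through.** **Inputs from section 2.9.** Anticipated bleeding is 14.5% (clopidogrel) and 21.2% (ticagrelor). Anticipated efficacy events are 18.9% per year (ticagrelor).

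**Input not in the document.** No 12-month mortality is given. I assume a range: 1–5% for deaths that compete with bleeding, and 0.5–3% for known noncardiovascular death.

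**The plan's own figure.** The article states no incidence corrected for death, so there is none to reproduce. The only figure built on the two bleeding rates is the safety power of about 87.1%. A one-sided 0.025 comparison of 14.5% with 21.2% at 655 per group gives 88.7%, or 87.3% with continuity correction. The rates are therefore used here as the plan uses them.

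**Formulas** (constant cause-specific hazards, time in years):
- Event hazard λ = −ln(1 − p), where p is the 12-month one-minus-Kaplan–Meier value.
- Death hazard μ = −ln(1 − d), where d is the assumed 12-month mortality.
- True cumulative incidence = λ/(λ + μ) × [1 − exp(−(λ + μ))] = λ/(λ + μ) × [1 − (1 − p)(1 − d)].

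**Worked case, d = 5%** (μ = 0.0513):
- Clopidogrel: λ = 0.1567, and 1 − 0.855 × 0.95 = 0.1878. Then 0.1567/0.2079 × 0.1878 = 14.14%, so 14.5% is 0.36 points too high.
- Ticagrelor: λ = 0.2383, and 1 − 0.788 × 0.95 = 0.2514. Then 0.2383/0.2896 × 0.2514 = 20.69%, so 21.2% is 0.51 points too high.

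**Bleeding, same mortality in both arms:**

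| Assumed mortality | Clopidogrel (KM 14.5%) | Ticagrelor (KM 21.2%) | Overstatement, points |
|---|---|---|---|
| 1% | 14.43% | 21.10% | 0.07 and 0.10 |
| 3% | 14.29% | 20.89% | 0.21 and 0.31 |
| 5% | 14.14% | 20.69% | 0.36 and 0.51 |

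**Efficacy composite at 18.9%**, with only known noncardiovascular death competing: at 0.5% the true incidence is 18.85% (overstated by 0.05 points), and at 3% it is 18.62% (overstated by 0.28 points).

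**Between-arm difference.** The Kaplan–Meier values differ by 21.2 − 14.5 = 6.70 points.
- Equal mortality of 1–5%: the true difference is 6.67 to 6.54, so 6.70 is too high by 0.03 to 0.16.
- 3% deaths on clopidogrel and 5% on ticagrelor: 20.69 − 14.29 = 6.40, so 6.70 is too high by 0.30.
- 5% deaths on clopidogrel and 3% on ticagrelor: 20.89 − 14.14 = 6.75, so 6.70 is slightly too low.

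The overstatement within each arm is assured. The sign of the error in the difference is not.

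**The case against.** The strongest case against acting is that nothing the trial will conclude depends on this.

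- **Tests.** Both hierarchical steps use the Cox hazard ratio. With deaths censored this is a legitimate cause-specific hazard ratio, and the Kaplan–Meier estimates do not enter it. This stands in full.
- **Size.** With 736 patients in an arm, the binomial standard error at 21.2% is √(0.212 × 0.788/736) = 1.5 points, three times the 0.5-point bias at 5% mortality. Table 1 also excludes malignancy, life expectancy under one year, cardiogenic shock and Killip III–IV, which argues for the lower part of the mortality range. This stands: the bias is small.
- **A biased risk difference.** A reader might infer that the reported absolute bleeding benefit will be inflated. The article does not support that. It plans a hazard ratio and no risk difference, and the error in any difference read off the curves can go either way. The Introduction itself cites lower cardiovascular mortality with ticagrelor in an earlier trial with aspirin, so equal mortality is not a safe premise.
- **All endpoints.** A reader might also infer that every secondary analysis is affected. Section 2.7 lists myocardial infarction, stroke and stent thrombosis as components of a composite that contains all-cause death, and no death competes with that composite. The problem arises only if components are analysed on their own, which the article does not define.
- **Detail left to the full plan.** An article need not spell out how competing deaths are handled. But here the article does state an estimator for a named quantity, and for bleeding the two do not match. A fuller plan that specified otherwise would contradict this sentence, so the objection does not remove the point.

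**Conclusion.** The point holds as a narrow, minor correction to descriptive reporting. For an endpoint that leaves out death from other causes, one minus Kaplan–Meier with deaths censored overstates the cumulative incidence in each arm. For bleeding this is about 0.1–0.4 points at 14.5% and 0.1–0.5 points at 21.2%. For the efficacy composite it is about 0.05–0.3 points at 18.9%.

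These sizes rest on mortality ranges that I assumed and on constant hazards. They also assume that deaths outside the endpoint are censored, which is the usual handling under Kaplan–Meier but is not stated. The direction within each arm does not depend on the constant-hazards assumption.

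Neither an inflated treatment difference nor any doubt about steps 1 and 2 follows from this.

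**What to change.** In section 2.9, replace the Kaplan–Meier sentence with Aalen–Johansen cumulative incidence for these endpoints, with any death not counted in the endpoint as the competing event:
- the primary bleeding endpoint;
- the efficacy composite, where noncardiovascular death competes;
- any secondary endpoint analysed without all-cause death.

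Keep Kaplan–Meier for the net-adverse-events composite. Keep the Cox model for steps 1 and 2, and describe its result as the cause-specific hazard ratio.

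The cost is close to nil. The estimator is available in SAS 9.4, the software named in the article, and cause of death is already needed for the efficacy endpoint. Sample size, significance level and data collection do not change. The one visible effect is that the reported incidences become slightly lower.

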### Randomization

2.3

Within 120 h of the new‐generation DES implantation, eligible patients will be randomized in a 1:1 ratio to receive either clopidogrel 75 mg daily or ticagrelor 90 mg twice daily in combination with dabigatran 110 mg twice daily for 12 months. The randomization will be done by the investigators through a central 24 h computerized randomization system of REDCap,^12^ using a random permuted block design with block sizes of four. The system can be accessed using personalized login data. Treatment allocation will be revealed for the patients and attending physicians.

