To evaluate the benefit‐risk balance, the primary endpoints of OPTIMA‐4 trial contain both safety and efficacy endpoints. The primary safety endpoint is set as major bleeding and CRNMB, which is consistent with the relevant RCTs,^5^, ^8^, ^9^, ^10^ and the primary efficacy endpoint in this trial includes both the cardiocerebrovascular and the peripheral vascular events. The anticipated incidence of major bleeding and CRNMB in each group and noninferiority margin ratio of efficacy endpoint are referred to the RE‐DUAL PCI trial, which contained DATT of dabigatran and a P2Y_12_ inhibitor of either clopidogrel or ticagrelor.^9^

The hierarchical statistical procedure is first based on the hypotheses that the clopidogrel group is superior to the ticagrelor group regarding the safety endpoint, and then noninferior to the latter regarding the efficacy endpoint. This design mainly concerns the major bleeding and CRNMB under DATT, which may result in unexpected discontinuation of antithrombotic agents and consequent increase of the ischemic risk.

The main inclusion and exclusion criteria are set on the basis of the following considerations. First, as only new‐generation DES is required to be implanted in this trial, and the high thrombotic risk scenario such as left main coronary artery DES implantation will be excluded, it would be acceptable to initiate DATT within 5 days after PCI, instead of after 1‐week  1‐month TATT. Second, because all enrolled patients will receive dabigatran‐based DATT, they need to meet the criteria of CHA_2_DS_2_‐VASc score ≥ 2 which indicates high risk of thromboembolism and requirement of anticoagulant. Third, patients with acceptable risk of bleeding (e.g., HAS‐BLED score ≤ 3) will be recruited, whereas those with high risk of bleeding will be excluded, considering the fact that 12‐month DATT has been recommended by current guidelines for the latter.^7^ Besides, previous studies enrolled patients with the average HAS‐BLED score ≤ 3 and showed the superiority of 12‐month NOAC‐based DATT.^5^, ^8^, ^9^, ^10^ Finally, valvular AF patients will not be enrolled owing to little evidence that NOAC is beneficial for these patients.^30^

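### The primary analysis set is called intention-to-treat but leaves out randomised patients who never take the assigned drug, in a trial where allocation is known before dosing

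*Protocol article*

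**What the plan says.** Section 2.9 introduces the full analysis set (FAS) "according to the intention‐to‐treat principle" and then defines it: "the FAS is defined as all patients being randomized who receive at least one dose of the assigned treatment". The per-protocol set (PPS) is described as a subset of the FAS. For the safety set (SS), "the SS includes all randomized patients with at least one safety assessment after randomization"; it carries no dosing condition.

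On use of the sets, Section 2.9 says: "The analysis of primary endpoints will be performed on both FAS and PPS, with FAS analysis as the primary analysis". It ends the paragraph with: "Safety analyses will be performed on the SS". The Discussion confirms that "the primary endpoints of OPTIMA‐4 trial contain both safety and efficacy endpoints".

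The same section makes bleeding superiority Step 1 of a hierarchy and efficacy noninferiority Step 2. Step 2 is not performed if Step 1 fails. Section 2.1 describes the trial as open-label, and Section 2.3 adds: "Treatment allocation will be revealed for the patients and attending physicians".

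**The concern.** Requiring a dose of the assigned drug is a condition applied after randomisation. The resulting set is a modified intention-to-treat set, whatever it is called. Read literally, it leaves out two kinds of patient: those who never start, and those switched to the other P2Y12 inhibitor before any dose of the one assigned.

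In a blinded trial such exclusions can hardly depend on the arm. Here patient and physician know the allocation before the first dose, and the Introduction itself voices concern about bleeding when ticagrelor is combined with an oral anticoagulant. Non-starting that differs between arms is therefore plausible, and it would enter both confirmatory tests. The PPS cannot repair this because it lies inside the FAS. The SS may pick up bleeding in some never-dosed patients, but it does nothing for efficacy.

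A smaller matter is the closing sentence on the SS. The Step 1 endpoint is both a primary endpoint and a safety endpoint, and that sentence makes no exception for it.

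**Working it through.** **1. The plan's own figures.** Inputs from Section 2.9: 18.9% annual efficacy rate, margin ratio 1.38, one-sided alpha 0.025, power 80%, 11% loss, bleeding 14.5% versus 21.2%.

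- A score test for a ratio of proportions, with 0.189 in both arms, gives 654.4, hence 655 per arm, as stated.
- 655 / (1 − 0.11) = 735.96, hence 736 per arm and 2 × 736 = 1472, as stated.
- Bleeding power at 655 per arm is 88.7%, or 87.3% with continuity correction, against the stated 87.1%.

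This point disputes none of these figures.

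**2. Who is in which set.**

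| Randomised patient | FAS | PPS | SS |
|---|---|---|---|
| Never takes the assigned drug, has a safety assessment | no | no | yes |
| Never takes the assigned drug, no safety assessment | no | no | no |
| Takes one dose, has a safety assessment | yes | if eligible and adherent | yes |
| Takes one dose, no safety assessment | yes | if eligible and adherent | no |

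The first two rows have no place in any stated efficacy analysis.

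**3. Illustrative size.** The article gives no non-starter rate. Assume that a fraction *f* of the ticagrelor arm never starts and is dropped, that nobody is dropped from the clopidogrel arm, and that the dropped patients have half or double the arm's average risk. With 736 randomised per arm, the rate left in the ticagrelor FAS is

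p_FAS = (p − f × p_dropped) / (1 − f).

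*Step 1, no true bleeding difference.* Take p = (14.5% + 21.2%) / 2 = 17.85% in both arms. The chance of declaring superiority is 1 − Φ(1.96 − d/SE), where d = p_FAS − p and SE = √[p(1 − p)(1/736 + 1/(736(1 − f)))]. For f = 5% at half risk:

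- p_FAS = (0.1785 − 0.05 × 0.08925) / 0.95 = 0.1832
- d = 0.0047, SE = 0.0202
- result 0.042

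*Step 2, true hazard ratio at the margin.* The ticagrelor rate is 18.9%; the clopidogrel rate is 1 − 0.811^1.38 = 0.2511. The chance of declaring noninferiority is Φ(ln(1.38/HR_FAS) × √D/2 − 1.96), with D the events in the FAS. For f = 5% at half risk:

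- p_FAS = (0.189 − 0.05 × 0.0945) / 0.95 = 0.1940
- HR_FAS = ln(1 − 0.2511) / ln(1 − 0.1940) = 1.341
- D = 736 × 0.2511 + 699.2 × 0.1940 ≈ 320
- result 0.0445

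| f | Step 1, half risk | Step 1, double risk | Step 2, half risk | Step 2, double risk |
|---|---|---|---|---|
| 1% | 0.0277 | 0.0202 | 0.0281 | 0.0196 |
| 2% | 0.0308 | 0.0161 | 0.0315 | 0.0152 |
| 3% | 0.0342 | 0.0127 | 0.0354 | 0.0116 |
| 5% | 0.0420 | 0.0077 | 0.0445 | 0.0064 |

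The nominal value is 0.025 throughout. Values above it favour clopidogrel; values below it work against clopidogrel. Excluding patients from the clopidogrel arm instead would reverse the directions.

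**4. After the fix.** The required number does not change. If all 736 per arm are analysed at the stated rates, power is about 92.0% for Step 1 and about 84.3% for Step 2 (ratio score test).

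**The case against.** The strongest reply is that the effect may be negligible. Patients are randomised within 120 hours of stenting, so never taking a single dose may be rare, and dropping such patients is a common convention. The first part stands as a limit on size. The convention is weaker support here, because allocation is open and the text claims the intention-to-treat principle. One could add that including never-dosed patients can dilute a true difference, which is not conservative for noninferiority. The PPS analysis already serves that purpose.

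Four stronger readings are tempting, and the article does not support them.

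- A reader might infer that every event before the first dose is lost. The definition governs membership, not the start of the clock, and the Abstract has follow-up running 12 months from randomisation. An event is lost only if the patient never takes a qualifying dose.
- A reader might infer that the whole two-drug regimen must have begun, so that the wait for dabigatran until heparin stops (Section 2.5) creates exclusions. The text asks for one dose. Dabigatran is common to both arms, and the natural reading is a dose of the assigned P2Y12 inhibitor, although the text does not say which drug counts.
- A reader might infer that the bias favours clopidogrel. If frailer, higher-risk ticagrelor patients fail to start, the ticagrelor arm looks better and both tests become harder to pass, as the double-risk columns show.
- A reader might infer that the Step 1 population is undecided. Section 2.9 puts the primary endpoints on the FAS as primary, and the Discussion says these include safety. The sentence on the SS can be read as covering other safety data; Section 2.8 lists adverse events separately from endpoints. What remains is a lesser ambiguity, since no exception is written.

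**Conclusion.** The point holds. The primary set does not match the principle claimed for it, and in this open-label trial the exclusions can depend on the arm in both confirmatory tests, with no stated efficacy analysis that restores the missing patients.

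Size and direction are unknown. The error ranges of roughly 0.008 to 0.042 for Step 1 and 0.006 to 0.045 for Step 2 rest on assumed one-sided exclusion of 1% to 5% (about 7 to 37 of 736 patients) with halved or doubled risk. They show what the definition permits; they do not predict what will happen. The SS sentence is a secondary wording defect. It matters mainly because Step 1 decides whether Step 2 is tested.

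**What to change.** In Section 2.9:

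- Define the FAS as all randomised patients, analysed as allocated, with time counted from randomisation.
- State that Step 1 (bleeding) and Step 2 (efficacy) are both tested on this set as primary.
- Keep a dosed-only set, if wanted, as supportive alongside the PPS, and say which drug's dose counts for it.
- State that the SS serves adverse events and a supportive bleeding analysis, not the Step 1 test.

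The cost is wording only. The sample size stays at 1472. Section 2.8 already follows all subjects and Section 2.7 already provides blinded adjudication of the primary endpoints, so no new data are needed. The change should be made before results by arm are known.

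Reporting the number of never-dosed and pre-dose-switched patients by arm would show how much the choice of set mattered.
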